### Assessment Instruments

The Iowa Infant Feeding Attitudes Scale (IIFAS), developed by Mora et al. (1999), is a reliable and valid tool used to determine maternal attitudes toward infant feeding and is included in the MAQ. The validated Breastfeeding Self-Efficacy Scale developed by Dennis and Faux (1999), is an instrument used to determine breastfeeding confidence. The shorter version, the Breastfeeding Self-Efficacy Scale-Short Form (BSES-SF; Dennis, 2003) is included in the MAQ.

Maternal secretory activation status can be assessed by maternal self-reporting of symptoms of secretory activation using the Assessment of the Onset of Lactogenesis II originally developed by Chapman and Pérez-Escamilla (2000). Maternal self-reporting of secretory activation has been shown to be a reliable indicator of secretory activation when compared with the gold standard method of test weighing an infant before and after breastfeeding to ascertain secretory activation (Rocha et al., 2020).

The ACE Study uses a version of the two-question Assessment of Onset of Lactogenesis II adapted by Demirci et al. (2023) for use in their pilot study to determine the feasibility and potential benefits of ACE in a small sample of United States mothers. Demirci et al. determined time of secretory activation by asking participants at 1–2 weeks postpartum: “How long did it take your milk to "come in” after your baby was born (i.e., when did you notice a big increase in the amount of milk)?” Demirci et al. adapted the assessment to minimize the cumulative participant survey burden in the early postpartum period. Answer options were also adapted from a by-hour recall to a by-day recall as Demirci et al. anticipated it would be difficult for participants to recall details 1–2 weeks after birth. In the ACE Study participants are asked at the 1-week postpartum questionnaire: “How long did it take your milk to “come in” after your baby was born (i.e., when did you notice a big increase in the amount of milk and a feeling of breast fullness)?” Answers are recorded to the nearest day, that is, “1 day or less,” “2 days,” “3 days,” “4 days,” “more than 4 days,” “my milk never came in,” “I don’t remember when my milk came in.” Mothers who report that their milk came in ≤ 1 day will be considered to have early secretory activation, milk onset at 2 days, or 3 days postpartum will be considered normal secretory activation, and onset at 4 days, or more than 4 days postpartum will be considered delayed secretory activation (> 72 hr postpartum). All participants repeat the BSES-SF at 4 weeks postpartum.

## Planned Data Analysis

Data will be analyzed using SPSS (Version 29) or R. The primary outcome variable is EBF4M postpartum (yes or no). The secondary outcome variables are any or exclusive breastfeeding (at 1/4/8/12/16 weeks postpartum—analyzed separately), supplementation with a human milk substitute in the hospital (yes or no), time of secretory activation (≤ 1 day, 2–3 days, or > 3 days postpartum) which are all dichotomous. Other outcome variables are infant admission to SCN (yes or no; dichotomous) and gestational age at birth (continuous). Any or exclusive breastfeeding at 1, 4, 8, 12, and 16 weeks postpartum, use of human milk substitutes in hospital, infant admission to SCN (dichotomous outcomes), and time of secretory activation (nominal outcome) will be assessed (and reported) both using unadjusted analysis (a basic comparison of proportions) and using an adjusted analysis (mixed-effects logistic regression, adjusted for maternal age, socioeconomic status, mode of delivery and potentially other hypothesized confounders). Gestational age at birth (continuous outcome) will similarly be assessed (and reported) both using unadjusted analysis (Student’s *t* test) and adjusted analysis (mixed effects linear regression, if modeling assumptions are met adjusted for maternal age, socioeconomic status, and potentially other confounders). The mixed effects models will incorporate a site variable both as a fixed effect, addressing any inter-site differences, and as a random effect, accounting for any inherent within-site correlation in the data resulting from the clustered design. The decision to include variables as confounders for adjustments in the models is based on both hypothesized and established (from related literature) relationships with the outcomes and variables of interest. An analysis of variance (ANOVA) test will be used to compare two models, one within and one without a site, by intervention interaction variable. If the model with the interaction term is deemed to be a better fit, then only pre-specified subgroup analysis will occur, which is a per-site analysis using the same models as described above. Missing data will be reported (as count and percentage) by variable and group. If problematic, multiple imputation (by chained equations) will be used to impute missing values, with reported effect estimates then calculated by pooling across models run on imputed datasets. A level of significance of *p* < 0.05 will be used, and the research team will use confidence intervals to give context to outcome variability.

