## Methods

### Research Design

The ACE Study is a stepped-wedge cluster (nested) randomized controlled, investigator-blinded, multicenter, non-inferiority trial with parallel intervention groups. The rationale for this trial design (Phase 1, a period where the control group data will be collected, and Phase 2, randomization of participants to either the midwife [MW] or video instruction [VI] groups) was chosen as it provides a quarantined period of observation and data collection from the control group. Randomizing participants to all three groups simultaneously was not performed as this would risk contamination (via artificially increasing knowledge above standard care) in the control group and hospital staff delivering care. Pregnant individuals attending the same antenatal classes may discuss and share aspects of their care, and hospital staff may inadvertently promote ACE to the control group. Each hospital (site) is a cluster, with the Phase 1 start time being dependent on hospital logistics (for example ability to carry out staff training, ethics, and governance approvals). During Phase 2, nested within each cluster, individual participants are randomized (50:50) to one of two invention arms. The trial has a primary endpoint of 4 months postpartum, specifically the rate of EBF4M. All enrolled participants will have data collected until 4 months postpartum. The endpoint in this trial was chosen as a timepoint where the achievement of the proposed level of breastfeeding would be significant, given previous national indicators (Australian Bureau of Statistics, 2017–2018).

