### Sample Size

The research team has used a control group estimate for the primary outcome, EBF4M, of 27% based on the Australian National Infant Feeding Survey (Australian Institute of Health and Welfare, 2011). This represented the best available, nationally representative breastfeeding data at the time of study design.

The research team hypothesized that an EBF4M rate of 45% will be achieved in both intervention groups. An alpha of 0.05 has been selected for the sample size calculations as (1) the tests are one-sided and (2) there are two primary hypothesis tests to be carried out. An *n* of 271 per group will be required to have over 80% power to detect a difference between the MW and VI groups, independently, as well as the control group. This will demonstrate superiority by a margin of at least 5% based on a difference in proportions using the normal approximation with an intraclass correlation of 0.01. With this *n* (271) in both the MW and VI groups, and assuming a rate of 45% will be observed for EBF4M within both intervention groups, the trial will have 80% power to demonstrate non-inferiority with a lower equivalence rate of 32%; based on the difference in proportions using the normal approximation. This lower equivalence rate was deemed acceptable as it represents the same increase over the control group as the primary analysis (i.e., 5%). Data will be analyzed based on the principles of intention to treat and per-protocol analysis, with non-inferiority concluded if both analyses produce the same results (Angeli et al., 2020; Tripepi et al., 2020). A loss to follow-up rate of 15% is anticipated; therefore, the research team estimates that 315 pregnant individuals will be recruited into each group to achieve sufficient follow-up data for analysis. Rolling recruitment across multiple hospital sites will be required to achieve the recruitment target of 945 participants.

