## Interventions

### Sequence Generation

The research team is using phased randomization (implemented via the stepped-wedge design), where an observation control group is recruited before commencing the intervention phase at each trial site. During Phase 2 at each trial site, participants have equal opportunity to be randomized into either the MW or VI groups. The randomization process is done using an online program for minimization (via QMinim) to ensure a balance of participants in intervention groups based on the chosen balancing variables. Two different balancing variables are used, maternal age (< 30, ≥ 30 years), and socioeconomic status (low, medium, high; determined by postcode and education level). The biased coin approach (*P* = .7; default in QMinim) is used to determine group allocation.

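### The unadjusted control-versus-ACE tests ignore hospital, although hospitals are the clusters and the sample size allows for an intraclass correlation of 0.01; the planned mixed models are not affected

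*Protocol article*

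**What the plan says.** Research Design sets the unit of clustering: "Each hospital (site) is a cluster, with the Phase 1 start time being dependent on hospital logistics". Sequence Generation describes a design "where an observation control group is recruited before commencing the intervention phase at each trial site", so each hospital supplies both control and ACE participants. In Phase 2, "individual participants are randomized (50:50) to one of two invention arms" within each hospital.

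Sample Size arrives at 271 per group, "based on a difference in proportions using the normal approximation with an intraclass correlation of 0.01".

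Planned Data Analysis gives two reported analyses. Breastfeeding at the follow-up weeks, in-hospital use of human milk substitutes, special care nursery (SCN) admission and secretory activation "will be assessed (and reported) both using unadjusted analysis (a basic comparison of proportions) and using an adjusted analysis" by mixed-effects logistic regression. Gestational age "will similarly be assessed (and reported) both using unadjusted analysis (Student’s" t test) and by a mixed-effects linear model. Site is named only as a term of the mixed models, where its stated purpose is to handle site differences and within-site correlation. One significance level, p < 0.05, is stated for everything, and the section does not say which of the two results decides. The abstract names adjusted logistic regression for the breastfeeding outcomes.

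**The concern.** The article accepts that participants from one hospital are correlated, sizes the trial for it and models it in the adjusted analysis. It then specifies tests that treat all participants as independent and pool over hospitals.

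Two things can go wrong in the pooled control-versus-ACE comparison. If the control:ACE ratio differs between hospitals, hospital differences leak into the ACE effect. If a hospital's own rate shifts between its two phases, that shift is counted as if it were individual-level noise. The article rules out neither. Phase 1 starts depend on local logistics, no ratio per hospital is fixed, and recruitment began in September 2019 with the last endpoint expected in April 2025. The hospitals differ: the Setting section gives socioeconomic deciles from 1 to 10 and caesarean rates from 23% to 49%.

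The outcomes exposed are those that Table 4 compares between control and ACE: in-hospital substitute use, secretory activation, SCN admission and gestational age. Exclusive breastfeeding at 4 months (EBF4M) joins them if the 16-week item in the analysis section stands for it. At stake is a reported significant result that reflects hospital mix or a change between phases and not ACE, with nothing in the analysis section to say that the other result takes precedence.

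**Working it through.** **Inputs from the article.** Sample Size gives a "control group estimate for the primary outcome, EBF4M, of 27" per cent, and the team "hypothesized that an EBF4M rate of 45% will be achieved in both intervention groups". It also gives a 5-point margin, one-sided alpha 0.05, over 80% power, ICC 0.01 and 271 per group. Combined ACE is therefore 542.

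**Assumed.** The number of hospitals in the calculation (4 to 7; seven are listed as proposed), the control:ACE ratios per hospital, the correlation between a hospital's two phases, and a two-sided 5% test.

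**1. The plan's own figure.**
- Without clustering: n = (1.645 + 0.842)² × (0.27×0.73 + 0.45×0.55) / (0.18 − 0.05)² = 162.6 per group.
- With 4 hospitals per group: 271/4 = 67.75, design effect 1 + 66.75 × 0.01 = 1.6675, and 162.6 × 1.6675 = 271.2.

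This matches 271. The 4 is inferred; with 7 hospitals the power at 271 would be 86%, still over 80%. Either way, 271 is well above the 163 needed for independent data.

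**2. Error of the plain test.** Let ρ be the ICC, c the correlation between a hospital's phases (cluster autocorrelation), and w0, w1 the hospitals' shares of the control and ACE groups. The true variance divided by the variance that the plain test assumes is

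R = [(1−ρ)(1/n0+1/n1) + ρc·Σ(w0−w1)² + ρ(1−c)(Σw0²+Σw1²)] / (1/n0+1/n1),

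and the two-sided error is 2[1 − Φ(1.96/√R)]. With n0 = 271 and n1 = 542, 1/n0 + 1/n1 = 0.005535.

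**3. Equal ratios, stable hospital effects** (w0 = w1, c = 1). R = 0.99, error 4.9%. Simulation (20,000 runs, common rate 35% assumed): 4.9% with 4 hospitals, 5.1% with 7. There is no inflation.

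**4. Ratios that differ, stable effects.** The simulated pattern was strong. With 4 hospitals, controls were 27, 54, 81, 108 and ACE 216, 162, 108, 54. Then Σ(w0−w1)² = 0.20, R = 1.35 and the formula gives 9.2%. A similar gradient over 7 hospitals gives R = 1.16 and 6.8%.

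| Simulated | Plain test | Stratified by hospital |
|---|---|---|
| 4 hospitals | 8.8% | 5.2% |
| 7 hospitals | 7.0% | 5.1% |

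A separate simulation gave about 6.4% plain and 4.8% stratified. The range is therefore about 6-9%, and stratification restores about 5%. At an assumed ICC of 0.05, the pattern in the table gives 24% and 14% plain, and about 5% stratified.

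**5. Equal ratios, hospital-by-phase variation.** For c = 0.5 and 4 equal hospitals, R = 0.99 + (0.01 × 0.5 × 2/4)/0.005535 = 1.44, error 10.3%.

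| Cluster autocorrelation | 4 hospitals: formula (simulated) | 7 hospitals: formula (simulated) |
|---|---|---|
| 0.8 | 7.0% (7.1%) | 6.1% (6.0%) |
| 0.5 | 10.3% (10.1%) | 7.9% (7.6%) |

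The stratified test has practically the same error here (7.1% and 10.2% with 4 hospitals; 6.1% and 7.6% with 7), so a site term does not cure this part. With unequal ratios and autocorrelation 0.8 together, the plain test has 10.9% (4) and 8.0% (7), and the stratified test 6.7% and 6.1%.

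**6. Midwife versus video.** With the same simulation and 1:1 allocation within hospital, the plain test has 5.3% (4) and 5.1% (7). This contrast is not materially affected.

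**The case against.** The strongest reply is that the design is already respected where it counts. A mixed model with site is reported for each of these outcomes, and the abstract names adjusted logistic regression for the breastfeeding outcomes. A crude comparison labelled unadjusted, printed beside it, is common practice. This stands, and it confines the point to the unadjusted results. It does not remove the point, because the analysis section itself specifies the plain tests, reports them under the same threshold and gives no order of precedence.

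The scope must also be narrow. Tables 1 and 4 define exclusive breastfeeding at 1 to 16 weeks as midwife versus video, randomized within hospital. The sentence that assigns the plain test does not name EBF4M. That the primary outcome is affected is therefore conditional on reading the 16-week item as EBF4M.

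A reader might infer from the design effect of 1.67 that the plain test's standard errors are always too small, with errors of 12.9% (one ACE arm versus control) or 15.4% (combined ACE versus control, 4 hospitals). The documents do not support that. Those figures need zero correlation between a hospital's two phases, as in a parallel cluster trial, whereas here each hospital supplies both sides. The number of hospitals is not given either.

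Finally, hospital-by-phase variation is not peculiar to the crude test; a model with only a site term shares it.

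**Conclusion.** The point holds for the unadjusted control-versus-ACE results only: their p-values and intervals can be wrong because hospital is left out. At the plan's ICC of 0.01 and a two-sided 5% level, the error is about 5% in the benign case, about 6-9% if control:ACE ratios differ between hospitals, and about 6-10% with moderate hospital-by-phase variation taken alone. These ranges rest on 4 to 7 hospitals, the ratio patterns shown and autocorrelations of 0.8 to 0.5, all assumed; a larger ICC would widen them. The planned mixed models do include site, and midwife versus video is not materially affected. This is a modest inconsistency that is cheap to correct, and it does not show that the trial's main conclusion would be unsound.

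**What to change.** In Planned Data Analysis:

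- For control-versus-ACE outcomes, define unadjusted as free of participant covariates but accounting for hospital: a Cochran-Mantel-Haenszel comparison stratified by hospital, or a model with group and site only. For gestational age, use a linear model with group and site.
- Give raw proportions and means as description, without p-values.
- State, in line with the abstract, that the site-accounting adjusted model carries the conclusion.

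This changes wording only and needs no new data or participants. The cost is slightly more analysis work and possibly slightly wider intervals. It removes the distortion from unequal ratios but not hospital-by-phase variation.

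A hospital-by-phase term with a small-sample correction is a separate option with a real power cost, and is not part of this fix. If the whole ICC were hospital-by-phase variation, at 27% versus 45% with 4 hospitals, the squared standard error is 0.99(0.1971/271 + 0.2475/542) + 0.01(0.1971 + 0.2475)/4, so SE = 0.0478 and 0.18/0.0478 = 3.77. Normal-approximation power is 96.5% (98.9% with 7 hospitals). With a t reference on the number of hospitals minus one degrees of freedom (assumed), it falls to about 71% with 4 hospitals and 94% with 7.

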## Background

Exclusive breastfeeding is when the infant receives only human milk, except for oral medicines, vitamins, and minerals, and it is recommended for the first 6 months of life (World Health Organization [WHO] & the United Nations Children’s Fund [UNICEF], 2021). Supplementation with human milk substitutes (like commercial infant formula) during the initial hospital stay after birth is common in Australia, with approximately one-third of infants receiving human milk substitutes during the birth hospitalization (Netting et al., 2022). Supplementation with human milk substitutes jeopardizes exclusive breastfeeding practices and increases the risk of early breastfeeding cessation (McCoy & Heggie, 2020; Vehling et al., 2018). As an alternative to the use of human milk substitutes, colostrum can be expressed in pregnancy, stored in a freezer, and taken to the hospital at the time of birth. Colostrum expressed in pregnancy can be defrosted and fed to infants during the initial hospital stay if additional supplementation is required. Supplementation with a parent’s own colostrum instead of human milk supplements may protect exclusive breastfeeding practices in hospitals.

Historically, there have been concerns that antenatal colostrum expression (ACE) can affect hormones that promote the onset of labor (e.g., oxytocin). To date, there has been only one large-scale and high-quality randomized controlled trial (RCT) of ACE conducted among pregnant individuals with low-risk diabetes (the Diabetes and Antenatal Milk Expressing [DAME] study). The DAME trial demonstrated that ACE twice per day for up to 10 min beginning at 36 weeks gestation was safe for pregnant individuals with diabetes who were otherwise at low risk of pregnancy or general health complications. In the DAME trial, there was no difference observed between randomization groups for admissions to the Neonatal Intensive Care Unit (NICU) or mean gestational age at birth (Forster et al., 2017).

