## Data Collection and Monitoring

### Antenatal Period

All participants receive a health check via telephone between 35 and 36 weeks gestation. An ACE Study researcher administers the short health check survey to determine if a participant has developed any health conditions during pregnancy that are part of the exclusion criteria. After completion of the health check survey, participants in the intervention groups receive the ACE intervention between 36 and 37 weeks gestation. For participants in the VI group, the ACE instruction is illustrated in the ACE video where information is delivered by an IBCLC. VI group participants receive the link to the video via email. The study midwives/IBCLCs delivering the one-on-one instruction are provided with a written overview of the relevant ACE information to discuss with participants prior to conducting an instruction session. Study midwives/IBCLCs are provided with a checklist to complete during each instruction session to ensure all teaching points are covered, and the ACE technique has been demonstrated with either a knitted breast or hands-on assistance and practice (if the participant agrees). The checklist is available in the online Supplemental Material.

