#### Antenatal Colostrum Expression Instruction

Intervention group participants are instructed to commence hand expressing from 37 weeks gestation, twice a day for 3–5 min per breast (maximum 10 min), using the accepted breast expression technique detailed below (Australian Breastfeeding Association, 2023). Participants are instructed to begin by stroking the breast towards the nipple and gentle breast massage to help stimulate the milk ejection reflex. Further instruction is given to make a “C” shape with the thumb and index finger and place approximately 3–4 cm on either side of the nipple, pressing in towards the chest and then pressing the fingers together and gently rolling fingers forward, being careful not to squeeze or pinch the nipple. Participants are advised to repeat the process to build up a rhythm, rotate the position of the fingers and thumb around the areola, and repeat the expressing technique to stimulate and remove colostrum from different parts of the breast. Participants are advised that small drops of colostrum may glisten on the nipple and can be collected using a sterile syringe. Participants are informed colostrum may not bead on the nipple and are reassured that this is not an indicator of potential breastfeeding ability or postpartum milk production.

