During pregnancy, participants complete the mothers’ antenatal questionnaire (MAQ) online, which is used to collect demographic information, maternal health information, breastfeeding intentions, maternal attitudes towards infant feeding, and breastfeeding self-efficacy.

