Time from starting ACE (obtained from expressing diaries) until labor	Expressing diaries/medical data	Difference, between the control group and intervention groups combined (MW and VI) in time from starting ACE until labor
Gestational age at birth	Medical data	Difference, between the control group and intervention groups combined (MW and VI) in gestational age at birth
Infant admission to SCN	Medical data	Difference, between the control group and intervention groups combined (MW and VI) in the proportion of infants admitted to the SCN

*Note*. ACE = antenatal colostrum expression; MW = midwife; VI = video instruction; SA = secretory activation; SCN = special care nursery; IgA = Immunoglobulin A; EGF = epidermal growth factor; TGF = transforming growth factor; MAQ = mothers’ antenatal questionnaire; IIFAS = Iowa Infant Feeding Attitudes Scale; BSES-SF = breastfeeding self-efficacy – short form.

Potential confounders identified a priori include maternal education, BMI, smoking, living in cities (Moss et al., 2020), maternal attitudes towards breastfeeding (Cox et al., 2015), and paternal breastfeeding support (Davidson & Ollerton, 2020).

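### The adjusted breastfeeding models fix mode of delivery as a covariate, although delivery follows the ACE instruction whose effect is being estimated

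*Protocol article*

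**What the plan says.** The Planned Data Analysis section of the protocol article lists the outcomes for its logistic models, starting with "Any or exclusive breastfeeding at 1, 4, 8, 12, and 16 weeks postpartum, use of human milk substitutes in hospital", followed by special care nursery (SCN) admission and time of secretory activation. Each is analysed twice: as an unadjusted comparison of proportions, and in a mixed-effects logistic regression "adjusted for maternal age, socioeconomic status, mode of delivery and potentially other hypothesized confounders". The model for gestational age at birth is described separately as "adjusted for maternal age, socioeconomic status, and potentially other confounders", without mode of delivery.

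On timing, the Antenatal Period section states that "participants in the intervention groups receive the ACE intervention between 36 and 37 weeks gestation", and the instruction section that "Intervention group participants are instructed to commence hand expressing from 37 weeks gestation".

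On a possible path from ACE to delivery, the Background notes that "there have been concerns that antenatal colostrum expression (ACE) can affect hormones that promote the onset of labor". Outcomes/Measurement and Table 4 list post-term induction, time from starting ACE to labour, gestational age at birth and SCN admission as outcomes ACE might influence.

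On confounders, the text after Table 4 says: "Potential confounders identified a priori include maternal education, BMI, smoking, living in cities", and goes on to maternal attitudes and paternal support. Mode of delivery is not named there.

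**The concern.** The primary aim asks what advising and teaching ACE does to exclusive breastfeeding compared with standard care. That is a total effect, whatever route it takes. A confounder of that effect must be settled before, or independently of, the instruction. Mode of delivery is not: every participant delivers after the point at which instruction is given.

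Two things can go wrong when such a variable is held constant. If ACE changes how women deliver and delivery affects breastfeeding, the adjusted coefficient drops that part of the effect. If an unmeasured obstetric factor influences both delivery and breastfeeding, conditioning on delivery also links ACE to that factor and can create an association where none exists.

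The same covariate list applies to SCN admission, which is in effect a safety outcome. Any harm that arose through labour and delivery would be partly adjusted away there.

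**Working it through.** No stated figure depends on the covariate list, so there is none to reproduce. The check sets out the order of events and then asks how large the distortion could be.

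**Order of events.** Instruction 36 to 37 weeks; expressing from 37 weeks; birth and mode of delivery; in-hospital feeding, secretory activation and SCN admission; breastfeeding at 1 to 16 weeks. Mode of delivery lies between the intervention and every outcome in the logistic models.

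**Inputs from the protocol.** Exclusive breastfeeding at 4 months (EBF4M) of 27% in controls and 45% with ACE (Sample Size), a total risk difference of 18.0 points and an odds ratio of (0.45/0.55)/(0.27/0.73) = 2.21. Caesarean rate 34%, the figure for one site; listed rates run from 23% to 49% (Setting).

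**Assumed inputs, not in the protocol.** Odds ratio of Caesarean for EBF4M of 0.7, 0.5 or 0.4. Change in Caesarean rate caused by ACE of −10 to +10 points.

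**Model.** logit P(EBF4M) = b0 + bA·ACE + ln(OR)·Caesarean. b0 is set so that controls average 27%, and bA so that the ACE groups average 45%. The delivery-adjusted risk difference compares ACE with control at one common Caesarean rate, c = (control rate + 2 × ACE rate)/3, because there are two ACE groups per control group.

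**One case in full: OR 0.5, Caesarean 34% rising to 39%.**
- b0 = −0.784: control EBF4M is 31.34% without and 18.58% with Caesarean; 0.66 × 31.34 + 0.34 × 18.58 = 27.0.
- bA = 0.847: the ACE figures are 51.56% and 34.74%; 0.61 × 51.56 + 0.39 × 34.74 = 45.0.
- c = (0.34 + 2 × 0.39)/3 = 0.373.
- Adjusted difference = 0.627 × (51.56 − 31.34) + 0.373 × (34.74 − 18.58) = 18.7 points, against a true total of 18.0.

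**All cases: adjusted risk difference in points (true total 18.0).**

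| Caesarean–EBF4M OR | −10 | −5 | 0 | +5 | +10 |
|---|---|---|---|---|---|
| 0.7 | 17.3 | 17.6 | 18.0 | 18.4 | 18.7 |
| 0.5 | 16.6 | 17.3 | 18.0 | 18.7 | 19.4 |
| 0.4 | 16.2 | 17.1 | 18.0 | 18.9 | 19.8 |

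Columns are the change in Caesarean rate due to ACE. For a 5-point change the error is 0.4 to 0.9 points; at the extremes of the table it is 1.8. The direction depends on whether ACE lowers or raises the Caesarean rate. Risk differences are used because the conditional odds ratio differs from 2.21 even with no bias (2.22 to 2.28 in the zero column).

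**Collider case.** In a simulation of 2,000,000 records, ACE had no effect on breastfeeding and Caesarean had none either, but an unmeasured factor affected both Caesarean and breastfeeding (assumed log odds +0.8 and −0.8). With an ACE-to-Caesarean log odds ratio of +0.3 or −0.3, the delivery-adjusted odds ratio was 1.03 or 0.97; with +0.6 or −0.6 it was 1.07 or 0.95. The unadjusted odds ratio stayed at 1.00.

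**The case against.** **An unadjusted result is reported as well.** True, and for the randomised comparison of midwife with video instruction it targets the total effect. It does not rescue the primary contrast. There, Phase 1 controls are compared with later Phase 2 participants, so some adjustment is needed, and the Abstract presents adjusted logistic regression as the analysis.

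**The path from ACE to delivery is unproven.** The Background also reports that the one large randomised trial found no difference in mean gestational age. Caesarean rate is not a listed outcome, and nothing in the article says that induction or labour timing changes it. This limits the expected size but does not make delivery a baseline variable, and the protocol treats effects on labour as open.

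**Caesarean practice may drift between phases, and some Caesareans are planned before 37 weeks.** Both are fair reasons to look at delivery in a sensitivity analysis. The covariate as described does not separate planned from later Caesareans.

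**The sentence does not name EBF4M.** Correct. It names exclusive breastfeeding at 16 weeks, which is the same visit but which Tables 1 and 4 assign to midwife versus video. Applying the covariate list to the primary model is an inference.

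**A reader might go further and say the important confounders are left to post hoc choice.** The article does not support that. It names confounders in advance and gives the basis for selection, and a final list may sit in an analysis plan that is not shown. The absence of mode of delivery from the list after Table 4 also proves little, since that list is not worded as complete.

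**Conclusion.** The point stands in limited form. The article fixes, by name, a covariate determined after the intervention in models meant to estimate the effect of that intervention. For breastfeeding at 1 to 16 weeks, substitute use, SCN admission and secretory activation this is what the text says; for EBF4M it is a reasonable inference.

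The size is modest: about 0.4 to 0.9 points on 18 for a 5-point shift in Caesarean rate, and zero if ACE does not affect delivery. The effect of Caesarean on breastfeeding, the effect of ACE on Caesarean and the unmeasured factor are all assumptions. A reader might infer that the trial's main result would be seriously wrong; nothing in the article or in these calculations supports that. The case for change is that the fault is clear and easy to remove.

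**What to change.** Remove mode of delivery from the main adjusted models, and say explicitly whether the same covariate set applies to EBF4M. If delivery is of interest, report a model that includes it as a sensitivity analysis, labelled as conditioning on a post-intervention variable.

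Adjust the main models for maternal age, socioeconomic status and those confounders already named after Table 4 that are fixed before allocation and actually collected, for example education, BMI, smoking and city living. Education already enters the socioeconomic variable used for minimisation, so the overlap should be settled. Paternal support should be listed only if it is collected, which the article does not show.

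The antenatal questionnaire records "breastfeeding intentions, maternal attitudes towards infant feeding, and breastfeeding self-efficacy", but the attitude (IIFAS) and self-efficacy (BSES-SF) scores should not be added as baseline covariates without qualification. Table 3 places both after allocation, Phase 2 participants are told their arm once they have consented, and Tables 1 and 4 list both as outcomes.

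The cost is wording in the analysis plan, with no new data and no change in sample size. It should be settled before group allocation is unblinded for analysis.
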